#### Inclusion criteria

The inclusion criteria for this study are as follows: current nonspecific LBP persisting for at least three months, consulted a medical doctor during the last month because of the persistent LBP, aged between 18 and 65 years, sufficient fluency in Dutch to follow treatment instructions and answer survey questions (Table 1).

**Table 1 Tab1:** **Inclusion criteria**

Inclusion criteria	Rationale
18 to 65 years old	Chronic low back pain in older adults is more likely to have specific causes (e.g., spinal canal stenosis)
Current nonspecific low back pain persisting ≥ 3 months	Condition studied is specifically chronic
Consulted a doctor during the last month for persistent low back pain	Back pain severe enough and motivation from the patient itself to seek treatment
Dutch fluency sufficient to follow treatment instructions and answer survey questions	Fully informed consent and data collection

#### Exclusion criteria

The exclusion criteria for this study are as follows: spinal canal stenosis, spondylolisthesis and spondylitis, large herniated disc sciatica, radiating pain below the knee, previous back surgery, a history of known spinal fractures, malignancy, known muscle-, nerve-, skin-, or joint diseases, pregnancy and lack of consent (Table 2).

**Table 2 Tab2:** **Exclusion criteria**

Exclusion criteria	Rationale
Spinal canal stenosis	Back pain possibly due to, specific disease
Spondylolisthesis	
Spondylitis	
Large herniated disc sciatica	
Radiating pain below the knee	
Previous back surgery	
History of vertebral fracture	
Malignancy	
Muscle-, nerve-, skin- or joint diseases	
Known pregnacy	Pregnancy-related low back pain is different in etiology and time course than the target condition for the study (nonspecific chronic low back pain)
Lack of consent	Research policy

### Measurements

#### Baseline testing

The Modified Oswestry Disability Questionnaire (MODI) score will be used as the primary (dependent outcome measure). The MODI is a disease-specific questionnaire to measure disability in LBP patients. The modified version of the Oswestry Disability Questionnaire replaces the sex life item with an employment or homemaking item and has an excellent reliability and good construct validity [21–23]. As secondary (independent) outcome measures the following tests are used:Measurement of impairments: duration of the LBP, pelvis impairments and respiratory impairments (all three items through anamnesis). Prone instability test, straight leg raise, beighton scale, active straight leg raise, sitting knee extension test, waiters bow, pelvic tilt, side support test, extensor endurance test, active sit-up and visual analogue scale for pain (VAS).Measurement of limitations in activities and participation: hours of physical activity per week (trough anamnesis). Short Form 36 Health Survey (SF36), Roland Morris Disability Questionnaire (RMDQ).Measurement of contextual factors: gender, age, height, weight, body mass index, smoking, profession, underwent previous therapy and comorbidity (trough anamnesis), Tampa scale for kinesiophobia and Fear Avoidance Belief Questionnaire (FABQ),

We performed a literature search to select all used clinical tests based on their reliability and validity [24]. Further, clinical tests used by Hicks *et al*. [16] were also included in our study design. The baseline testing takes about 30 minutes.

#### Follow-up

Short-term follow-up will take place after completion of the treatment program at nine weeks. All primary and secondary outcome measures from the baseline testing will be reevaluated at this time point.

Long-term follow-up will take place at six months and one year after entering the study. The following outcome measurements will be inventoried: age, weight, hours of physical activity per week, profession, duration of LBP, MODI, Tampa scale for kinesiophobia and VAS. The patients will initially be contacted by mail, and by phone if they do not respond to the mail within two weeks to make an appointment (Table 3).

**Table 3 Tab3:** **primary (dependent) and secondary (independent) outcome**

Measures	0 weeks	9 weeks	6 months	1 year
***Primary outcome:***				
MODI	X	X	X	X
***Secondary outcome***				
***Impairments:***				
Duration low back pain*	X	X	X	X
Pelvis impairments*	X	X		
Respiratory impairments*	X	X		
PIT	X	X		
SLR	X	X		
Beighton scale	X	X		
ASLR	X	X		
SKET	X	X		
Waiters bow	X	X		
Pelvic tilt	X	X		
Side support test	X	X		
Extensor endurance test	X	X		
Active sit up	X	X		
VAS*	X	X	X	X
***Secondary outcome***				
***Activities and participation:***				
RMDQ	X	X		
SF-36	X	X		
Hours physical activity/week*	X	X	X	X
***Secondary outcome***				
***contextual factors:***				
Tampa scale	X	X	X	X
FABQ	X	X		
Gender*	X			
Age*	X	X	X	X
Height*	X			
Weight*	X	X	X	X
BMI*	X	X		
Smoking*	X	X		
Profession*	X	X	X	X
Previous therapy*	X			
Comorbidity*	X	X		

**Information obtained through anamnesis.*

*MODI: modified oswestry disability questionnaire, PIT: prone instability test, SLR: straight leg raise, ASLR: active straight leg raise, SKET: sitting knee extension test, VAS: visual analogue scale, RMDQ: roland morris disability questionnaire, FABQ: fear avoidance belief questionnaire, BMI: body mass index.*

### Randomization and blinding

In both phases patients will be randomly assigned to one of the three treatment groups after baseline testing. The responsible researcher will use a randomization list generated with Microsoft Excel® software (version 14.3.9, Microsoft Corporation, Zaventem, Belgium). Physiotherapists responsible for the treatment sessions are blinded for the results of baseline and follow-up measurements, which are being performed by the responsible researcher.In the validation phase a pre stratification will be used to ensure a 50:50 ratio between matched and unmatched therapy within one intervention group. Patients who have a strong preference for one of our intervention groups and therefore cannot be randomized will be asked to participate in a parallel cohort study. In this study similar baseline and follow-up measurements will be used.

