**Methods/Design:**

The study design is a randomized controlled trial. Patients with nonspecific CLBP of more than three months duration are recruited at the Antwerp University Hospital (Belgium) and Apra Rehabilitation Hospital. After examination, patients are randomly assigned to one of three intervention groups: motor control therapy, general active exercise therapy and isometric training therapy. All patients will undergo 18 treatment sessions during nine weeks. Measurements will be taken at baseline, nine weeks, six months and at one year. The primary outcome used is the Modified Oswestry Disability Questionnaire score. For each type of exercise therapy a CPR will be derived and validated. For validation, the CPR will be applied to divide each treatment group into two subgroups (matched and unmatched therapy) using the baseline measurements. We predict a better therapeutic effect for matched therapy.

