#### Validation phase

In the validation phase the intervention therapy stays the same, but new patients will be included. In this study design, the interest is that treatment success will be higher in the matched group than the unmatched group, which means a one-tailed hypothesis is used to calculate the power. In the validation phase we need 105 patients to detect a minimum clinically important difference (effect size 0.43) with 80% power using a one-tailed hypothesis. This means that three groups of 35 patients are needed to complete the whole trial. Again we assume a dropout rate of 54% into account and therefore aim to include 229 patients.

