### Data analysis

#### Derivation phase

This phase aims to detect potential predictive variables for treatment success (dichotomous, yes or no) in a set of baseline measurements. A minimal decrease in the MODI score of six points is considered as treatment success [35].

Potential predictive variables are selected as follows: first, individual variables from the self-reports, history and physical examination are tested for their bivariate association with the reference standard using independent sample t tests, Mann-Whitney U tests or chi-square tests based on the nature of the data. Variables with a significance level of *P* <0.10 are retained as potential prediction variables. We chose a more liberal significance level at this stage to avoid excluding potential predictive variables.

Next, selected potential prediction variables and known predictors as determined in the study of Hicks *et al*. [16] are entered into a multiple linear regression equation to determine the optimal set of predictors. A significance of *P <*0.05 is used in this stage. Variables retained in the regression model are used to develop a multiple CPR for classifying patients as likely responders to treatment. This statistical analysis is performed for each treatment group (motor control therapy, general active exercise therapy and isometric training therapy).

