#### Validation phase

In the validation phase new patients will be again assigned randomly into one of the three treatment groups. Based on the derived CPR determined in phase one, each intervention group will be divided into either ‘matched therapy’ or ‘unmatched therapy’. The recruitment, information form, informed consent, measurements, blinding and intervention procedure will be the same for both derivation and validation phase.

To verify intergroup differences at baseline, variables will be compared between groups using independent t tests, Mann-Whitney U tests, or chi-square tests of independence based on the nature of the data.

To examine the principle hypothesis (difference in treatment effect between matched and unmatched groups), a three-way repeated-measures analysis of variance will be performed with treatment group (motor control versus general active exercise therapy vs. isometric therapy) and classification subgroup (motor control versus general active exercise therapy versus isometric therapy) as between-subject variables and time (baseline, nine weeks, six months and one year) as the within-subject variable. The dependent variable is disability (MODI score). The hypothesis of interest is the three-way interaction, and the two-way interactions between time and treatment group and between time and classification subgroup. We hypothesize that outcome over time will not differ based on the randomized treatment group, or the classification subgroup, but will depend on the interaction between the treatment group and classification subgroup, such that patients randomized to matched treatment will have better outcomes than patients randomized to unmatched treatment. This hypothesis will be supported if the three-way interaction is significant, but the two-way interactions are not. Pairwise *post-hoc* comparisons will be performed at each follow-up period to further explore any significant interaction terms. In both the derivation and validation phase we will use an intention-to-treat analysis.

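### Validation phase: three separate rules, one three-level class, three equal arms and a 50:50 matched split in each arm are not reconciled; as stated, the chance of matched therapy would generally differ by class

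*Protocol article*

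**What the plan says.** The protocol article states four features of the validation phase.

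- **Separate rules.** The abstract (Methods/Design) says "For each type of exercise therapy a CPR will be derived and validated". Under Data analysis, Derivation phase, variable selection and regression are run within each treatment group on its own.
- **A two-way split in each arm.** The abstract adds that "the CPR will be applied to divide each treatment group into two subgroups (matched and unmatched therapy) using the baseline measurements". Randomization and blinding says that "a pre stratification will be used to ensure a 50:50 ratio between matched and unmatched therapy within one intervention group".
- **Random assignment to three equal arms.** Data analysis, Validation phase: "In the validation phase new patients will be again assigned randomly into one of the three treatment groups". Power analysis, Validation phase, says "we need 105 patients to detect a minimum clinically important difference (effect size 0.43) with 80% power using a one-tailed hypothesis" and divides these into three groups of 35.
- **A three-level class in the model.** The repeated-measures analysis of variance takes treatment group and "classification subgroup (motor control versus general active exercise therapy versus isometric therapy) as between-subject variables", with time as the within-subject factor. The hypothesis rests on the three-way interaction.

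Study design also describes a direct comparison of treatment success between matched and unmatched patients.

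**The concern.** The model needs every patient in exactly one of three classes. Rules fitted separately in three arms are not built to be mutually exclusive or exhaustive, so they do not supply that class.

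Even with one class per patient, an exact half-and-half split inside three equal arms does not follow from random assignment. It has to be forced by allocation probabilities that depend on class. Matched and unmatched patients then differ in class mix, and a direct comparison mixes the effect of matching with the prognosis of the classes. That comparison is the purpose of the phase, and the allocation cannot be repaired once patients are randomised.

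**Working it through.** **Inputs.** From the article: three rules, three arms of 35 (N = 105), 50:50 within an arm. Not in the article, hence assumed and shown as ranges: how often each rule is positive, the class shares p₁, p₂, p₃, and the prognosis of each class.

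**Step 1: rules kept as separate yes/no rules.** If each rule is positive in a fraction q of patients, independently, then P(none) = (1−q)³, P(exactly one) = 3q(1−q)², and the rest meet two or more.

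| q | none | exactly one | two or more |
|---|---|---|---|
| 0.20 | 51% | 38% | 10% |
| 0.33 | 30% | 44% | 26% |
| 0.50 | 12.5% | 37.5% | 50% |

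Only those positive on exactly one rule have an evident level of the three-level factor. On this reading, class-blind allocation makes the matched share of an arm equal to q for that arm's rule, so 50:50 arises only if q = 0.50.

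**Step 2: one class per patient, class-blind 1:1:1.** The matched share in arm k is p_k. The shares sum to 1, so the average over arms is 1/3. The stated 50:50 is not reproduced. With p = 1/3 in every class, the chance of at least 17 matched among 35 is 4.4% in one arm, and 0.044³, about 0.009%, in all three.

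**Step 3: one class per patient, equal arms, 50:50 forced.** Each arm holds 1/3 of patients and half of them are matched, so the matched cell is 1/6 of all patients:

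- P(matched given class k) = (1/6)/p_k = 1/(6p_k).
- Feasibility needs p_k ≥ 1/6 to fill the matched cell. It also needs p_k − 1/6 ≤ 2 × 1/6, because the unmatched patients of class k must fit into the unmatched halves of the other two arms. Hence 1/6 ≤ p_k ≤ 1/2.
- The class mix is 1/3 each among matched patients and (p_k − 1/6)/(1/2) = 2p_k − 1/3 among unmatched patients.

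**Step 4: size of the confounding.** Suppose the commonest class differs by +δ MODI points in expected outcome, the rarest by −δ, and the middle one by 0. The matched mean shift is 0. The unmatched shift, which is the bias in an unadjusted comparison, is δ(2p_max − 1/3) − δ(2p_min − 1/3) = 2δ(p_max − p_min).

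| class shares (%) | P(matched given class) | unmatched class mix (%) | bias, δ = 2.5 | bias, δ = 5 |
|---|---|---|---|---|
| 33/33/33 | 0.50/0.50/0.50 | 33/33/33 | 0 | 0 |
| 40/35/25 | 0.42/0.48/0.67 | 47/37/17 | 0.75 | 1.5 |
| 50/30/20 | 0.33/0.56/0.83 | 67/27/7 | 1.5 | 3.0 |
| 60/25/15 | infeasible (third would be 1.11) | – | – | – |

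The 50/30/20 case lies on the upper limit. The first class's unmatched patients (0.500 − 0.167 = 0.333) fill the unmatched halves of both other arms (2 × 0.167). No second-class patient could then enter the third arm, or the reverse.

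**The case against.** The strongest reply is that random assignment need not mean class-blind 1:1:1, and that the announced pre-stratification may itself be class-weighted. This stands in part. With 2:1:1 within class and equally common classes, every arm is 50:50 without confounding. The same holds if arms are sized in proportion to class share and no class exceeds 1/2, for example 52.5/31.5/21 of 105 at 50/30/20%. A reader might therefore call the design self-contradictory or impossible, and the text does not support that. However, the first escape needs equal classes, the second gives up the equal groups of the power section, and shares are unknown until derivation ends.

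A reader might also infer that many patients have no matched status. On the yes/no reading each randomised patient is positive or negative on the rule for the arm received, so matched status exists. What is undefined is the level of the classification factor. The problems in Step 1 and Steps 3–4 belong to different readings and must not be added together.

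Nor is the planned principal test biased by 3 points. That figure belongs to an unadjusted comparison, whereas the analysis of variance includes class. Setting 3 points against the six-point success threshold would also mislead, because that threshold is a change within a patient.

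Finally, tie rules and allocation weights may sit in a fuller protocol, and the validation flow chart is not shown. That is fair for the operational detail. It does not answer the main point: the stated per-arm 50:50 with equal groups itself makes allocation depend on class unless classes are equally common.

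**Conclusion.** The point holds as a failure to reconcile four stated features, and it should be settled before validation recruitment. With separate rules, the model's classification factor is undefined for patients positive on none or several; under independence with 20 to 50% positive per rule, only about 38 to 44% meet exactly one. With one class per patient, equal arms and 50:50 per arm force a matched probability of 1/(6 × class share), feasible only for shares between 1/6 and 1/2.

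The resulting bias in the plain comparison described under Study design runs from zero with equal classes to about 3 MODI points at 50/30/20% and ±5 points. Its direction depends on which class has the better prognosis. Shares, independence and class prognosis are all assumptions. The planned model, once class is defined, removes class prognosis, though near the feasibility limits some treatment-by-class cells would be sparse or empty.

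**What to change.** Before the validation phase starts:

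1. Fix a rule that gives each patient exactly one class, for example the therapy with the highest predicted success from the derived models, with a stated tie rule.
2. Randomise within class strata with one ratio common to all classes. A ratio of 2:1:1 favouring the matched therapy gives P(matched) = 1/2 in every class, so 50:50 overall and no confounding of matching with class at any class mix.
3. In Randomization and blinding, replace the within-group 50:50 by an overall 50:50.
4. Adjust every matched-versus-unmatched contrast for class, including the direct comparison in Study design.

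The cost is a new randomisation list and some wording. Classing by highest predicted success is also a different kind of rule from three separate responder rules. Arm sizes and within-arm shares will follow the class mix: arm k holds p_k/2 + (1 − p_k)/4 = (1 + p_k)/4 of patients, so its matched share is 2p_k/(1 + p_k). At 50/30/20% this is 67/46/33%. The rarest class would then have about 0.5 × 0.20 × 105 = 10.5 matched patients, so the rule for a rare class is validated less precisely.

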### Intervention

During the nine-week intervention, patients will be treated two times a week. Patients will be assigned randomly into one of three intervention groups (motor control therapy, general active exercise therapy and isometric training therapy). Each intervention will take about 70 minutes. A 10 minutes warm up and cool down period will be the same in each treatment regime. Each group receives 50 minutes of therapy-specific intervention. Previously trained physiotherapists will give the treatment. To ensure that all therapists provide the same exercises, a treatment protocol for each treatment group was developed and a treatment diary will be filled out after each session. Interventions in the derivation and validation phase are similar.

#### Motor control therapy

The local stabilizing muscles (such as the multifidus, transversus abdominis, pelvic floor muscles and diaphragm) together with the global muscles (such as the erector spinae and rectus abdominis) are important in creating spinal stability [25–27]. An impaired spinal stability is considered an important factor in developing LBP [28–30]. This leads to the conceptualization of motor control therapy for the lumbar spine. Such therapy involves very specific low-load exercises of deeper trunk muscles that are dysfunctional in nonspecific CLBP [31, 32] and has proven to be effective in nonspecific LBP [4–7, 10].

Patients in this intervention group follow motor control training based on the work by Richardson and Hides [33]. There are three levels to be completed by the patients. To evolve to the next level the patient must be able to correctly execute each exercise described in the former level. However, if the patient is not able to do so in the first level within three weeks of treatment or after six sessions, we will automatically proceed to the second level with the intention to minimalize the drop out and maximize the patient’s compliance. The first level is based on the isolated contraction of the local motor control muscles. Contraction of the transversus abdominis is performed with low intensity controlled by palpation. The second level is based on the contraction of local and global motor control and global mobilizing muscles. In the third level patients will practice the contraction of local and global motor control and global mobilizing muscles in functional patient specific conditions (for example a patient who has to perform a lot of loaded trunk rotations during work will get specific exercises in a rotation movement direction, similar to the work condition) (Tables 4 and 5).

**Table 4 Tab4:** **exercise summary**

Treatment regimens:	Motor control therapy	General active exercise therapy	Isometric training therapy
***First phase MCT:***			
ADI in supine position	X		
ADI in sitting position	X		
ADI in sitting position 1DTM	X		
ADI in high squat position	X		
ADI in medium squat position	X		
ADI in supine position with heel lifts			
ADI in supine position with heelslide	X		
ADI with superman exercise	X		
ADI with top leg turn out	X		
***Second phase MCT:***			
ADI with side bridging	X		
ADI with back bridging	X		
ADI in sitting position 3DTM	X		
Hip extension	X		
Side-squat	X		
Reverse lunge	X		
Star excursion exercise	X		
***Third phase MCT:***			
ADI in functional movements	X		
Leg-press		X	
Leg-extension		X	
Calf raise		X	
Standing abduction		X	
Standing adduction		X	
Lat pull down		X	
Low row		X	
Triceps		X	
Biceps		X	
Chest press		X	
Shoulder press		X	
Fly		X	
Front raise		X	
Side raise		X	
Active sit up		X	
Hamstring stretch		X	
Quadriceps stretch		X	
Adductor stretch		X	
Latissimus dorsi stretch		X	
Trapezius stretch		X	
TD for lumbar flexion			X
TD for lumbar extension			X
TD for lumbar rotation			X
TD for lumbar lateroflexion			X
Stationary bike	X	X	X

*MCT: motor control therapy, ADI: abdominal drawing in, DTM: dimensional trunk movements, TD: Tergumed device.*

